### **Dependent variables:**

*primary clinical outcomes:*

- preferred gait speed (20 m walk test)
- stride length (at preferred speed and at 1.4 km/h)

*secondary clinical outcomes:*

- stride length variability (at preferred speed and at 1.4 km/h)
- stride time (at preferred speed and at 1.4 km/h)
- stride time variability (at preferred speed and at 1.4 km/h)
- step width (at preferred speed and at 1.4 km/h)
- step width variability (at preferred speed and at 1.4 km/h)

*feedback control variables (at 1.4 km/h):*

- $R^2$  (feedback model relating foot placement to centre of mass movement)
- RMS error (feedback model relating foot placement to centre of mass movement)
- Position gain (feedback model relating foot placement to centre of mass movement)
- Velocity gain (feedback model relating foot placement to centre of mass movement)

*neural correlates (at 1.4 km/h):*

- beta power during walking at preferred speed
- EEG-EMG coherence during walking at preferred speed

### **Analysis technique:**

Initially, independent t-tests and for EEG data cluster-based permutation tests time locked to the gait cycle will be used to compare patients to controls. The presence of and direction of differences between groups will facilitate interpretation for any effects found in analyses 2a - 2c. For this no corrections for multiple comparisons will be made. However, to present overall differences between groups we will reduce dimensionality of the set of primary and secondary clinical outcomes by means of PCA and use stepwise logistic regression on PC-scores to assess between group differences. For feedback control variables and neural correlates we will separately correct for multiple comparisons.

vi. SDTT vs. SDTT+ (2a)

Added value of additional component (SDTT+) to Speed Dependent Treadmill Training (SD Analysis technique.

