## 6. Statistics and analysis plan

### i. Sample size calculation

The sample size was calculated using the SampSize applicationon for the clinical primary objective (i.e., comfortable gait speed overground, measured in m/sec from a 20 meters walking test), with a significance level (alpha) of 0.05 and power (1-beta) of 0.80, with an allocation ratio of 1:1 in parallel groups. From the available literature, it is known that standard treadmill (SDTT) may improve comfortable overground gait speed up to 0.1 m/sec (from a baseline of 1.26 m/sec) in comparison to standard overground walking and that SDTT with perturbations (SDTT+) may further increase comfortable overground gait speed up to +0.08 m/sec in comparison to SDTT. Thus, we will assume that SDDT+ is superior to SDTT at improving comfortable overground gait speed based on an expected average difference in gait speed between the two groups of +0.08 m/sec with a SD of 0.08 Under this assumption, 17 subjects per group are expected to be enrolled, rising to 20.4 considering a maximum drop-out rate of 20%. This would lead to 41 subjects per trial, rounded to 42 to allow for groups of equal size.

Overall, 126 patients at all clinical sites will in enrolled over a period of 24 months. The recruitment totals for each site is outlined in Table 2. Given the time frame of the trial, recruitment will be monitored on a monthly basis. Should any site encounter recruitment difficulties, other sites have the capacity to recruit additional participants for each cohort as well as to recruit additional cohorts if necessary.

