## **v. Case-control study (1b)**

### **Population:**

21 (min. 17 for analysis) PD patients (To) randomly selected from total sample

21 (min. 17 for analysis) healthy controls age- and sex-matched to PD group

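### Healthy controls are matched to the PD group on age and sex, but analysis 1b compares them with independent t-tests that use neither factor, so the comparison is conservative to the extent that age and sex explain the outcome

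*Protocol*

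**What the plan says.** Section 6.v of the protocol defines two groups for analysis 1b. The patients are 21 (at least 17 analysed) "PD patients (To) randomly selected from total sample". The comparison group is "21 (min. 17 for analysis) healthy controls age- and sex-matched to PD group". The protocol does not say whether each control is matched to one patient or whether the two groups are balanced as a whole.

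Under the analysis technique of the same section, "Initially, independent t-tests and for EEG data cluster-based permutation tests time locked to the gait cycle will be used" for the comparison of the two groups. The results have a stated use: "The presence of and direction of differences between groups will facilitate interpretation for any effects found in analyses 2a - 2c". On multiplicity at this first stage: "For this no corrections for multiple comparisons will be made". A second step reduces the clinical outcomes to principal components and will "use stepwise logistic regression on PC-scores to assess between group differences". Neither step has a term for age, sex or matched pairs.

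Elsewhere the protocol does treat age as relevant. The mixed models in 6.vi and 6.vii adjust for potential confounders and name age and Hoehn and Yahr stage as examples.

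**The concern.** The test does not fit the way the controls are sampled. Once controls are chosen so that age and sex agree with the patient group, those factors no longer add to the chance variation of the difference in means. The independent t-test still estimates its standard error from the full within-group variance, including the part due to age and sex. The standard error is then too large, the confidence interval too wide and the true significance level below the nominal one.

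What is at stake is sensitivity. Section 6.ii explains that there is no placebo arm and that the comparison with people without PD is meant to help interpret the training effects. If a variable that is abnormal in PD is missed in 1b, a training-related change in it is harder to read as a move towards normal. With 17 to 21 per group there is little precision to give away.

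**Working it through.** **The plan's own figure.** Section 6.i gives a "significance level (alpha) of 0.05 and power (1-beta) of 0.80, with an allocation ratio of 1:1 in parallel groups", a difference of 0.08 m/s and an SD of 0.08 m/s, so d = 1.0. A two-sided, unpaired t-test (noncentral t) has power 0.781 at 16 per group and 0.807 at 17, so the stated 17 reproduces. This calculation is for the randomised comparison. Section 6.v uses the same 17 as its minimum but gives no effect size, SD or correlation for 1b.

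**Inputs for the check.**
- n = 17 or 21 per group (6.v).
- Two-sided 5% level. The 0.05 is from 6.i; two-sided is assumed because it reproduces the 17.
- R² is the share of within-group outcome variance explained by age and sex. It is not stated and is assumed to be 0 to 30%.
- A true PD-control difference of 0.8 SD (assumed).
- Matching balances age and sex between the groups. No pairs are required.

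**Formulas.** With within-group variance σ², the true variance of the difference in means under matching is 2σ²(1 − R²)/n. The independent t-test works with about 2σ²/n. Hence:
- interval width relative to what is needed: 1/√(1 − R²);
- real type I error: approximately P(|t| > t_crit/√(1 − R²)) on 2n − 2 degrees of freedom;
- adjusted model: noncentrality 0.8·√(n/2)/√(1 − R²) on 2n − 4 degrees of freedom.

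**Numbers in, n = 17, R² = 0.2.**
- Width: 1/√0.8 = 1.118, about 12% too wide.
- Critical value: 2.037 on 32 df. 2.037/√0.8 = 2.277, which has a two-sided tail probability of 0.030.
- Adjusted model: 0.8 × √8.5/√0.8 = 2.608 against a critical value of 2.042 on 30 df, giving power of about 71%.

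**Results.** Power is from simulation of group-level matching. The closed forms agree to within about one percentage point.

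| R² | Interval too wide by | Real type I error, n = 17 | Power at 0.8 SD, n = 17: independent vs adjusted | Power at 0.8 SD, n = 21: independent vs adjusted |
|---|---|---|---|---|
| 0% | 0% | about 5% | 62% vs 62% | 71% vs 71% |
| 10% | 5% | about 4% | 63% vs 66% | 73% vs 76% |
| 20% | 12% | about 3% | 64% vs 72% | 74% vs 81% |
| 30% | 20% | about 2% | 64% vs 76% | 75% vs 85% |

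**If matching were one to one and a paired test were used.** Degrees of freedom fall from 32 to 16 (n = 17) or from 40 to 20 (n = 21). The paired interval is narrower only if the within-pair correlation exceeds 1 − (t_crit,2n−2 / t_crit,n−1)², which is 0.077 at n = 17 and 0.061 at n = 21. With zero correlation the paired test loses power at 0.8 SD: 59% against 62% at n = 17, and 69% against 72% at n = 21.

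**The case against.** The strongest reply is that the size of any loss rests on a quantity the protocol does not give. If age and sex explain little, nothing is lost. Features of the design may keep the shared variance low: patients span Hoehn and Yahr I to III and come from four clinical centres, while controls are recruited in Amsterdam, so variation from disease severity and centre is not shared. This stands. The loss is conditional and has to be shown over a range.

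A second reply is that the wording on matching can mean balance at group level, in which case there are no pairs for the t-test to ignore. That also stands, and a reader should not infer from the protocol that matched pairs are being broken. It does not remove the point, because the table above was obtained without pairs.

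Third, the error is in the safe direction and 1b is supportive. A reader might infer that the t-test is invalid in the sense of too many false positives, or that PD abnormalities will necessarily be missed. The documents support neither. At the assumed shares the test is conservative, and at 0.8 SD the difference in power is between 0 and 12 percentage points. For a difference of 1.0 SD (assumed), unpaired power at 17 per group is already about 81%. No conclusion on SDTT against SDTT+ depends directly on this test.

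**Conclusion.** The point holds in a limited form. Section 6.v selects controls on age and sex and then fixes a test that uses neither. The consequence is a loss of precision that grows with the variance that age and sex explain: nothing at 0%, 3 points of power at 10%, 7 to 8 points at 20% and 10 to 12 points at 30%, for a 0.8 SD difference with 17 to 21 per group. Both the share and the effect size are assumptions. Larger losses could be computed from a high within-pair correlation such as 0.5, but nothing in the protocol supports that value or one-to-one pairing. This is a minor efficiency matter in an interpretive analysis. It is worth correcting because the adjusted model gives up essentially nothing even when age and sex turn out to be irrelevant.

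**What to change.** In 6.v, replace the independent t-tests with a linear model of each non-EEG outcome on group, age and sex, and report the adjusted group difference with its confidence interval. This is valid whether matching is individual or at group level, and it still works if drop-out to 17 breaks up pairs. State in the population paragraph which kind of matching is meant. A paired test should be an option only if matching is one to one, with the note that it halves the degrees of freedom, loses a pair whenever either member cannot be analysed, and loses power if the within-pair correlation is below about 0.06 to 0.08.

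The cost is a change of wording and two degrees of freedom (32 to 30 at 17 per group, 40 to 38 at 21). Year of birth and gender are already among the descriptive measures for trial participants, and the controls' age and sex must be known in order to match them.

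### Case-control analysis 1b: stepwise selection of PC scores brings back the multiplicity that the PCA step appears meant to handle

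*Protocol*

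**What the plan says.** Protocol section 6.v compares baseline PD patients with healthy controls. The samples are "21 (min. 17 for analysis) PD patients (To) randomly selected from total sample" and "21 (min. 17 for analysis) healthy controls age- and sex-matched to PD group", so 34 to 42 subjects in all. The outcomes are first compared one by one with independent t-tests (cluster-based permutation tests for EEG), and the protocol states: "For this no corrections for multiple comparisons will be made".

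For an overall comparison it continues: "we will reduce dimensionality of the set of primary and secondary clinical outcomes by means of PCA", and will then "use stepwise logistic regression on PC-scores to assess between group differences". Correction for multiple comparisons is promised separately for the feedback control variables and neural correlates. None is mentioned for the PC-score regression. The section gives no number of components, retention rule, direction of selection, entry or removal criterion, or significance level for this step.

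Section 6.ii describes the PD-versus-control comparison as an aid to interpreting effects in the PD group.

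**The concern.** The uncorrected t-tests are followed by a summary analysis that appears intended to avoid testing 13 outcomes separately. Stepwise selection undoes much of that. It tries each component against group membership, keeps those that pass, and reports the surviving model as the group difference. Ordinary p-values from that model take no account of the selection.

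Two things are at stake. If there were no group difference, the chance of reporting one would exceed the nominal level whenever two or more components are offered at p<0.05. If there is a difference, the selected model may include components that do not separate the groups, and these would be presented as features of PD gait when training effects are interpreted. The choice of stepwise regression is stated in the protocol. A statistical analysis plan could fill in its settings but could not replace it without departing from the protocol.

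**Working it through.** **Inputs from the protocol.**
- Subjects: 17 to 21 per group (6.v, Population).
- Variables entering the PCA (6.v, Dependent variables): gait speed (1), stride length at two speeds (2), and five secondary outcomes at two speeds (5 × 2 = 10). Total 1 + 2 + 10 = 13.
- Alpha: none is given for 1b. The 0.05 of section 6.i is assumed.

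**The plan's own figures.** The plan states no error rate for this step, so there is none to reproduce. The group sizes match section 6.i: with a difference of 0.08, SD 0.08, two-sided alpha 0.05 (sidedness assumed) and power 0.80, the normal approximation gives 16 per group and the t-based calculation 16.7, so 17. Then 17 × 1.2 = 20.4, rounded up to 21. These figures were derived for the randomised comparison and say nothing about the PC-score regression.

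**Simple approximation.** With k uncorrelated components each offered at 0.05 and no group difference, the chance that at least one enters is 1 − 0.95^k. For k = 3 this is 1 − 0.857 = 14.3%, for k = 4 it is 18.5%, and for k = 5 it is 22.6%.

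**Simulation under no group difference.** Thirteen normal outcomes were generated, with a correlation of 0.7 between the two speeds of one outcome and 0.2 otherwise (assumptions). They were standardised, PCA was run on the pooled sample, and forward logistic selection was applied to the first k components. A false positive means that at least one component enters. There were 4,000 replicates for likelihood-ratio (LR) entry with k = 3 to 5, and 2,000 for the other cells.

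| PCs offered | 1 − 0.95^k | LR p<0.05, 21 / 17 per group | Wald p<0.05, 21 / 17 | AIC, 21 / 17 |
|---|---|---|---|---|
| 1 | 5.0% | 5.1 / 5.7% | 3.2 / 4.0% | 15.4 / 15.9% |
| 2 | 9.8% | 10.7 / 10.6% | 7.7 / 6.9% | 29.6 / 29.9% |
| 3 | 14.3% | 16.1 / 16.3% | 11.6 / 11.6% | 44.5 / 45.1% |
| 4 | 18.5% | 20.7 / 21.7% | 13.8 / 14.5% | 52.4 / 52.3% |
| 5 | 22.6% | 25.8 / 26.5% | 19.1 / 17.2% | 60.6 / 62.6% |
| 6 | 26.5% | 30.8 / 29.4% | 23.4 / 19.5% | 69.0 / 68.4% |

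With a data-driven number of components, LR entry at 0.05 and four correlation patterns (1,000 replicates each), the rate was 10–26% for the eigenvalue-above-one rule, 26–37% for an 80% variance rule and 37–43% for a 90% variance rule.

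**When some components do differ.** This case was not simulated. By arithmetic, if one of five components differs and each of the other four has about a 5% chance of entry, at least one spurious component joins the model with probability of about 1 − 0.95^4 = 18.5%.

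**Alternatives on the same null data (k = 3, 4, 5; 4,000 replicates).**

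| Test | 21 per group | 17 per group |
|---|---|---|
| Hotelling T-squared | 4.8, 4.5, 5.0% | 4.6, 5.1, 4.9% |
| LR test of the full logistic model | 6.5, 6.8, 8.1% | 6.8, 8.1, 8.6% |

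**The case against.** The strongest reply has four parts.

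- **The settings are open.** The number of components, the entry rule and any adjustment of the selected model are normally left to the statistical analysis plan, which is not at hand. The protocol also does not say that entry of any component counts as a significant difference. This stands as a limit on the size. A reader might infer that the plan as written has a 16–26% error rate; it does not support that, because the figure needs three to five components and LR entry at p<0.05. With one component the rate is about nominal, and Wald entry gives lower rates. Nor should retention of all 13 components be used as an upper figure, since the stated purpose is to reduce dimension.

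- **The global null is unrealistic.** Section 3 describes short strides, slow gait and high step variability in PD, and inclusion requires a gait sub-score of at least 1. This also stands. It moves the weight of the concern from a false overall difference to spurious components alongside real ones, but does not remove it.

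- **Nothing hinges on the result.** Section 6.v ties the interpretation of analyses 2a–2c to the presence and direction of the group differences, which the t-tests address first. The PCA step only presents the overall difference. This is right and sets the severity.

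- **Bias in the coefficients.** A reader might add that selected coefficients are inflated by a material amount. No such size was calculated, so it is not claimed here.

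What the reply does not answer is that the protocol itself names stepwise selection as the means of assessing the overall difference and makes no allowance for it.

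**Conclusion.** The concern holds as a minor point. In 34 to 42 subjects, stepwise selection among PC scores is not a controlled test of an overall difference when two or more components are offered at p<0.05 under LR entry. The size depends on settings that the protocol does not give, on reading entry of any component as a difference, and on forward selection; backward elimination was not checked. Under Wald entry the excess also begins at two components, but it is smaller.

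If the groups truly differ, the consequence is roughly a 5% chance, per component that does not differ, of its being shown as a group difference. A reader might infer that the trial's main conclusions are affected. They are not: analysis 1b is supportive, and no randomised comparison uses the stepwise result.

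**What to change.** In section 6.v, replace the stepwise regression with one unpaired Hotelling T-squared test, consistent with the independent t-tests already planned, or with a permutation test. Apply it to a number of components fixed by a rule that ignores group, such as a stated share of cumulative variance. Report the group contrast for every retained component with its interval. Hotelling was checked here with three to five components; if the rule keeps more, the permutation version is the safer default.

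If stepwise selection is kept, state the number of components and the entry rule, and obtain its p-value by permuting group labels through the whole selection procedure. The asymptotic LR test of the full logistic model should not be offered as equivalent, because it ran at about 6.5–8.6% at these sample sizes.

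The cost is analysis wording only, with no new data or participants. The downside is that no reduced, selected model would be presented.

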**Dependent variables:**

*primary clinical outcomes:*

- preferred gait speed (20 m walk test)
- stride length (at preferred speed)
- stride length (at 1.4 km/h)

*secondary clinical outcomes (T1):*

- stride length variability (at preferred speed and at 1.4 km/h)
- stride time (at preferred speed and at 1.4 km/h)
- stride time variability (at preferred speed and at 1.4 km/h)
- step width (at preferred speed and at 1.4 km/h)
- step width variability (at preferred speed and at 1.4 km/h)
- falls (diary)
- timed-up-and-go (TUG) test
- 2-minute walk test
- MiniBESTest
- MOCA
- MDS-UPDRS, part III
- mGES

*secondary clinical outcomes (T2):*

- steps per day
- uninterrupted walk durations
- stride time variability
- symmetry

*feedback control variables (T1 all at 1.4 km/h):*

- $R^2$  (feedback model relating foot placement to centre of mass movement)
- RMS error (feedback model relating foot placement to centre of mass movement)
- Position gain (feedback model relating foot placement to centre of mass movement)
- Velocity gain (feedback model relating foot placement to centre of mass movement)

*neural correlates (T1 all at 1.4 km/h):*

- EEG beta power in(pre-)motor areas during walking at preferred speed
- EEG-EMG coherence during walking at preferred speed

Linear mixed effect models with the interaction of treatment and time in the model and a random intercept for participant nested within center (Twisk et al., 2018), controlling for relevant potential confounders (e.g., age, H&Y stage). For the EEG data, we will use cluster-based permutation tests time locked to the gait cycle.TT)

vii. Independent RCTs SDTT vs SDTT+ (3a)

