## 3. Background

Parkinson's disease (PD) affects over 10 million people worldwide and is one of the most prevalent neurodegenerative diseases. It is a multi-system neurodegenerative disorder, which among other symptoms causes severe and disabling motor deficits. One of these deficits, impaired gait, causes falls, a serious complication for people living with PD, even when managed with medication. Approximately 70% of people with PD experience falls each year. The consequences of falls include fractures, hospital admissions, increased caregiver burden, loss of independence, fear of falls, social isolation and early mortality. Falls are cited as one of the worst aspects of PD and unfortunately only few efficacious interventions are available. Non-pharmacological interventions in the form of exercise contribute to slowing disease progression and reduce fall risk through substantial improvements in gait quality, as reflected in increased speed and stride length and reduced gait variability.

Improving walking ability and preventing falls in people with PD is of critical importance to the world's aging population and health care systems globally. The importance of improving gait and preventing falls for people with PD and their communities is corroborated by our early stakeholder survey. This survey (used in the co-development of this project) included 294 people with PD, 76 family members, 16 clinicians and 29 caregivers. It revealed strong consensus regarding the imperative to develop effective gait training interventions that can improve walking ability, reduce fall risk; and increase quality of life. However, because of gaps in our mechanistic understanding, most exercise prescription fails to address the unmet needs and motor deficits specific to PD. People living with PD walk with short strides and consequently, at a slow speed, which is associated with poor general health. Their gait pattern is further characterized by a high variability of step characteristics, which is associated with falls.

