Participants will be asked to complete a daily diary via their personal smartphone or by paper pencil depending on their preference, including the following information: medication intake, physical activities performed, freezing of gait (FOG) episodes, falls experienced and information on fatigue. Other than the clinical assessment, that is performed during ON medication, the home assessment contains periods of ON, OFF, and transitions between phases, along with various contextual factors that influence mobility. To accurately evaluate the relationship between improvements in lab-based and daily-life gait outcomes, this diary records the influence of Parkinson's medication and physical activity on mobility during the home assessment and ensures with that comparability between the gait outcomes of To and T1. During the functional assessment, participants receive support in personalizing the diary by entering their medication schedule and adding typical physical activities. Over seven days, the diary is completed daily and is expected to take 1–3 minutes per day. Only deviations from the medication schedule need to be noted, while normal intake can simply be checked off for each day. Physical activities, FOG episodes, and falls can be logged by adding abbreviations/X marks in the provided timetable. Participants are encouraged to keep the diary beside their medication box to help prevent late entries, while no daily reminders will be sent to minimize the burden on participants.

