#### **B. Weekly Calendars**

Weekly online calendars will be used to assess:

- Physical activity both related to the study and other planned activities
- Falls adverse events
- Falls and injuries
- Mobility
- Fatigue
- Exercise Adherence both related to the study and other planned activities
- Health services use

Reported falls will be followed up with a phone call to assess severity and ensure ongoing participant safety.

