## **B. Clinical outcome measures**

- B1. Fall events (occurrence and frequency) and fall related injuries: The number of falls and whether the falls were injurious will be recorded. Twelve-month retrospective during To and during the duration of the trial.
- B2. Fracture history: Number and type of fracture sustained will be recorded. Twelve-month retrospective during To.
- B3. Medication: Current medication will be recorded at each visit.
- B4. Euro-Qol (EQ-5D): The EQ-5D measures quality of life. It consists of two components; health state description and evaluation. This will be completed on To, T1 and T2.
- B5. Frailty Index (FI): The FI measures frailty five different criteria (shrinking, low physical endurance/energy, low physical activity, weakness and slow walking speed). This will be completed at To, T1 and T2.
- B6. Functional Assessment of Chronic Illness Therapy (FACIT) Fatigue scale: The FACIT Fatigue Scale measures fatigue during usual daily activities over the past week. This will be completed at To, T1 and T2.
- B7. Visual Analogue Scale (VAS): The VAS will be used to determine the pain during rest and walking and the self-assessed quality of walking. This will be completed at To, T1 and T2.
- B8. Groll Functional Comorbidity Index (FCI): This is a self-administered test with physical function as the outcome. This will be completed at To.

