**Analysis technique:**

Linear mixed effect models with the interaction of treatment and time in the model and a random intercept for participant (Twisk et al., 2018), controlling for relevant potential confounders (e.g., age, H&Y stage). For the EEG data, we will use cluster-based permutation tests time locked to the gait cycle.

viii. Mechanisms underlying changes in gait performance (3b)

**Population:** 126 PD patients

Associations between clinical outcomes and feedback control

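### Falls, a count that is mostly zero, are put through a linear mixed model with no exposure term, and the protocol does not settle which instrument supplies them

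*Protocol*

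**What the plan says.** **Method.** Section 6.vi (2a) names falls, with the diary as source, as one of 12 secondary clinical outcomes at T1. The method for the whole list is "Linear mixed effect models with the interaction of treatment and time in the model and a random intercept for participant nested within center"; only EEG data are treated differently. Section 6.vii (3a) lists falls with no source, crosses time (T0, T1, T2) with group, and uses a linear mixed model with a participant random intercept. Section 6.iv (1a) lists diary falls among the variables given Bland-Altman limits of agreement and a paired t-test, and makes those limits the yardstick for effects in the 2a-2c comparisons.

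**Source.** The protocol describes falls in four ways:
- The home-assessment diary (sections 5.vii.B, 5.ix.B and 5.xi.B) records "freezing of gait (FOG) episodes, falls experienced and information on fatigue". Its window is one week: "Over seven days, the diary is completed daily and is expected to take 1–3 minutes per day".
- Section 5.x.B covers T1 to T2: "Weekly online calendars will be used to assess" falls and injuries, among other things. The Trial Summary and outcome G6 (section 5.xii.G) also assign falls to the weekly calendars.
- Outcome B1 (section 5.xii.B) defines the collection of falls as "Twelve-month retrospective during To and during the duration of the trial", and the safety section (5.xiii) likewise monitors them throughout.
- Analysis 3a gives no source.

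**Frequency.** The Background states: "Approximately 70% of people with PD experience falls each year".

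**The concern.** Falls over a short window are a non-negative integer, zero for most people, with a few patients contributing several. A Gaussian model with a treatment-by-time term returns a difference in mean counts with no reference to time observed. It cannot give a rate ratio, and its error distribution does not resemble the data. In 1a, limits of agreement computed on almost constant zeros are of no use as a yardstick.

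The choice of source matters as much. If diary means what it means everywhere else in the protocol, the comparison rests on one week of observation per visit, although about 12 weeks of calendar data are being collected. Falls motivate the trial in the Background, so a null result from a handful of events could be misread as evidence of no effect.

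**Working it through.** **The plan's own figures.** The protocol gives no sample size, event count or power for falls. Its calculation of 17 per group concerns gait speed. It reproduces (16.7 from the t-test formula with 0.08/0.08 = 1, 80% power and 5% taken as two-sided) and has no bearing on falls.

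**Inputs.**
- 70% with at least one fall per year (section 3).
- 126 patients (section 6.i). From Table 2, 11+21+21+10 = 63 intervention and 10+21+21+11 = 63 control.
- Diary window 7 days (section 5.ix.B).
- T1 to T2 interval 12 weeks ± 2, taken as 84 days (section 5.iv).
- Assumptions, not in the documents: a constant rate within a person; clustering described by a negative binomial with dispersion k = 1 to 3 (k = 0 is Poisson); the 70% applies to this population.

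**Step 1: annual mean count m that gives 70% with at least one fall.**
- Poisson: m = -ln(0.30) = 1.204.
- Negative binomial: m = (0.30^(-k) - 1)/k, giving 2.33 (k=1), 5.06 (k=2) and 12.01 (k=3).

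**Step 2: scale to each window.** Multiply by 7/365.25 or 84/365.25. The share with no fall is exp(-m) for Poisson and (1 + k·m)^(-1/k) otherwise, with m now the mean for the window.

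| k | Mean per patient, 7 days | Falls in 126, 7 days | Patients at zero, 7 days | Falls in 126, 12 weeks | Patients who fall, 12 weeks |
|---|---|---|---|---|---|
| 0 | 0.023 | 2.9 | 97.7% | 34.9 | 30.5 |
| 1 | 0.045 | 5.6 | 95.7% | 67.6 | 44.0 |
| 2 | 0.097 | 12.2 | 91.5% | 146.5 | 56.9 |
| 3 | 0.230 | 29.0 | 83.9% | 348.1 | 66.1 |

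The ratio of expected falls is 84/7 = 12 in every row. At a constant rate, 2.9 falls means about 1.5 per arm. In the 21 patients of 1a, a 7-day window would hold 21 × 0.023 = 0.5 falls (Poisson) to 21 × 0.230 = 4.8 (k=3).

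**Step 3: information on a treatment effect.** Assume the rate is halved, with 63 per arm and window means m0 and m1 = m0/2. The standard error of the log rate ratio is sqrt[(1/m0 + k)/63 + (1/m1 + k)/63], and power is Φ(ln 2/SE - 1.96). The formula is rough when events are very few.
- Poisson, 7 days: SE = sqrt[(43.3 + 86.7)/63] = 1.44, power 7%. The 95% interval runs from the estimate divided by 16.7 to the estimate multiplied by 16.7.
- Poisson, 12 weeks: SE = sqrt[(3.61 + 7.22)/63] = 0.415, power 39%. The corresponding factor is 2.25.
- Over k = 0 to 3: 7% to 24% with the diary, 39% to 57% with the calendars.
- With 50 per arm (20% dropout): 6% to 20% and 32% to 48%.

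**Step 4: does a Gaussian comparison reject too often?** A two-sample t-test served as a simple proxy for the mixed model on simulated 7-day counts with equal rates (63 per arm, 20,000 runs). It rejected in 2.4% (Poisson), 4.4% (k=1) and 4.9% (k=2) of runs. Skewness of the counts was about 4 to 7. There is no sign of excess false positives.

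**The case against.** **What stands on the other side.**
- That the diary in 2a and 1a is the seven-day home diary is an inference. The protocol uses the word for nothing else, and the outcome is placed at T1, before the calendars are described. Yet G5 omits falls from the self-reports at T0 and T1, and G6 and the Trial Summary give falls to the calendars. The event counts above are therefore conditional on the diary reading.
- About 3 falls is the constant-rate figure. Under strong clustering it is up to about 29.
- Falls are one of 12 T1 secondary outcomes and appear in none of the four numbered objectives. The primary endpoint is gait speed.
- The distribution for one secondary outcome is often refined in a SAP. Here, however, the protocol's own statistics section names a method for the list, and that method does not suit this entry.

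**Stronger readings that the documents do not support.**
- A reader might set B1's 12-month recall at T0 against shorter later windows and infer a spurious decline: at an unchanged Poisson rate, 1.20 against 0.28 (12 weeks) or 0.02 (7 days), an apparent drop of 77% to 98%. No section says the recall enters as the T0 value of the repeated measure. Under the diary reading the windows are seven days at every visit and the artefact disappears. Even with unequal windows, equal fall rates shift both arms alike, so the expected treatment-by-time interaction stays zero.
- A reader might infer that the calendars are the only prospective fall data. B1 and the safety section cover the whole trial, training included.
- A reader might infer that the calendars are excluded from every model. Since 3a names no source, that is not established.

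**Conclusion.** The point holds as a correction to a secondary analysis. The protocol prescribes a linear model without exposure time (2a, 3a) and Bland-Altman limits with paired t-tests (1a) for a zero-heavy count, and it is inconsistent about where that count comes from. If the seven-day diary is the source, expect about 3 falls in 126 patients at a constant rate, or about 6 to 29 under k = 1 to 3, with roughly 84% or more of patients at zero. The 12-week calendars give 12 times as many expected falls on the same assumptions.

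The cost is a badly fitting model, no interpretable rate ratio and little information. Type I error inflation and bias in the treatment-by-time effect are not shown, and nothing here touches the gait-speed conclusion. The sizes rest on the protocol's 70% applying to the enrolled patients, a constant rate within each person, and the assumed dispersions. The mismatch between model and outcome depends on none of these.

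**What to change.** 1. State one source for the falls outcome and bring sections 6.iv, 6.vi and 6.vii into line with the Trial Summary, B1 and G6. If the calendars were always meant, the word diary in 1a and 2a, and the T1 label in 2a, still need changing.
2. Remove falls from the linear-model lists in 2a and 3a and from the Bland-Altman list in 1a.
3. Add one paragraph: calendar-recorded falls from T1 to T2 are analysed by negative binomial regression with treatment, centre, H&Y stage and the T0 12-month fall history as covariates and log(days observed) as offset; the rate ratio is reported with its 95% confidence interval. The offset also handles the ± 2-week visit window and early withdrawal.
4. Use seven-day diary falls for description only.

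**Cost.** One paragraph and one model, with no new data. The comparison moves from T1 to the T1-T2 period, when both groups are offered the home walking programme, and falls during training are left to safety reporting. Power remains below 80% for an assumed halving of the rate (39% to 57% with 63 per arm), so the result should be presented as an estimate with its interval.
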